### *8.2.1 SMS/USSD-Based Surveys (Population for Objective 1)*

The target population (those we seek to sample from) for SMS/USSD-based patient experience survey are patients currently in care, aged 18 years or older, and have access to a mobile device (i.e. owned or shared). We will seek to enrol a convenience sample of about 250-300 eligible participants (depending on the overall clinic size) to receive SMS/USSD-based surveys at each facility during each six-month period during the intervention. During clinic visits, patients will be approached by study staff using a recruitment script to determine their eligibility and voluntary willingness to participate. If they agree to participate they will have their contact information and ART number collected, and thereby be enumerated for objective 1. Patients who were enrolled in the prior 6 months and completed the SMS/USSD-based survey will maintain enrolment for the remainder of the study period. Based on pilot data survey response rate of 40% completion, this sample will allow us to collect 75-100 new complete surveys per facility per measurement period (each six months) and estimate the patient experience with a precision of approximately +/-10%. In essence the SMS population will represent a nested sub-cohort within the larger clinic population in that they will be queried more than once.

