|------------|-------|-------|------------------------------------------------------------------------------------------------------------------------------------------------------------------------------------------------------------------|-------------------------------------------------------------------------------------------------------------------------------------------------------------|----------------------------------------------------------------------------|
| SMS survey | +     | +++++ | SMS will be critical due to speed and reach. In addition, it will allow for potential capture of care experiences that occur in community that are not captured by exit surveys in facility based models of care | Up to average 200 measurements in each of approximately 34 facilities in each of the four study periods (200 * 34 * 4) for total maximum of 27,200 measures | Proportion of patients who agree to, receive, initiate and complete survey |

|                                     |    |     |                                                                                                                                                                                   |                                                                                                                                                                                  |                                                                                                                                                                                                                                    |
|-------------------------------------|----|-----|-----------------------------------------------------------------------------------------------------------------------------------------------------------------------------------|----------------------------------------------------------------------------------------------------------------------------------------------------------------------------------|------------------------------------------------------------------------------------------------------------------------------------------------------------------------------------------------------------------------------------|

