#### 8.3.1 SMS/USSD-Based Surveys. (Data Collection for Objective 1)

After enrolling for SMS/USSD-based surveys, participants will be automatically sent SMS/USSD-based surveys every 3 months. Participants will receive automated disbursements of varying amounts of airtime (zero Kwacha to five Kwacha) incentive for survey completion allowing us to understand strategies to optimize response rates. Participants will also receive up to 3 reminders if survey not initially completed. To measure implementation of SMS/USSD-based surveys, we will collect data on 1) the number of patients who are approached, eligible, and agree to participate; 2) the number of surveys successfully sent, initiated, completed; 3) time to response and the number of reminders sent, and 4) socio demographics among those who agree to participate.

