### *8.5.1 SMS/USSD-based Surveys (Analysis of implementation in Objective 1)*

We will describe the acceptance to participate in the SMS/USSD-based survey as a proportion of those approached that enrol as well as survey completion rate among those enrolled. In addition, we will analyse response by sociodemographic characteristics, message method (short message service and unstructured supplementary service data), and mobile network operator (of which there are currently three in Zambia) using univariate and multivariate regression models, using log link functions, and random effects to account for clinic correlations. We will estimate the precision of the SMS/USSD-based survey tool as a function of total complete responses and clinic population. Time to survey response and the role of reminders on survey completion rate will also be evaluated using time to event approaches such as the Kaplan Meier method or Aalen Johansen if competing risks are identified.

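### The SMS/USSD completion rate mixes new enrolees with retained past completers, and the response models allow for clinic but not for repeated surveys of the same person

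*Combined protocol and SAP*

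**What the plan says.** Protocol 8.2.1 plans to "enrol a convenience sample of about 250-300 eligible participants" at each facility in each six-month period, and then states: "Patients who were enrolled in the prior 6 months and completed the SMS/USSD-based survey will maintain enrolment for the remainder of the study period". It describes the panel as a "nested sub-cohort within the larger clinic population in that they will be queried more than once". Its precision target of about ±10% counts 75 to 100 new completed surveys per facility per period, and cites the pilot: "Based on pilot data survey response rate of 40% completion".

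Protocol 8.3.1 sets the frequency: "participants will be automatically sent SMS/USSD-based surveys every 3 months".

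Protocol 8.5.1 describes uptake through the proportion enrolling and the "survey completion rate among those enrolled". It analyses response by sociodemographic characteristics, message method and network operator, using regression with "random effects to account for clinic correlations". It also says that precision will be worked out from the total number of completed responses and the clinic population. New and retained participants are not distinguished, and no participant-level term is named. Table 2, under 8.2.5, gives the implementation metric as "Proportion of patients who agree to, receive, initiate and complete survey". The SAP contains no SMS analysis.

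**The concern.** The condition in 8.2.1 has a purpose only if completing a survey decides who stays, so it implies that non-completers leave. From Period 2 onward the people being surveyed are then a mix of fresh enrolees and people selected for having responded before. A single completion rate over that mix describes neither group. It exceeds the rate among new enrolees whenever some patients are more inclined to respond than others. Section 8.5.1 itself expects such differences, since it plans to look for predictors of response.

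Separately, a person may be surveyed up to eight times in 24 months. A model with clinic effects only treats those responses as independent within clinic. Predictors that are fixed or nearly fixed for a person, such as sex or network operator, then get standard errors that are too small. Precision computed from the total number of responses has the same weakness.

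The plan handles repeats elsewhere. SAP 5.2 uses individual-level and facility-level random effects for repeated visits, and the RIAS analysis in protocol 8.6 clusters at provider and facility.

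At stake is an Objective 1 implementation metric: how well the SMS survey was taken up, and by whom.

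**Working it through.** **The plan's own figure.** The 95% half-width at a proportion of 0.5 is 1.96 × √(0.25/n). This gives 9.8% for n = 100 and 11.3% for n = 75, so the stated ±10% reproduces. It counts new completes only, so the retained panel does not enter it. (The enrolment target at the pilot rate gives 250 × 0.40 = 100 to 300 × 0.40 = 120 completes, not 75 to 100. These figures should be reconciled separately.)

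**Inputs.** From the documents: 40% completion (8.2.1), four six-month periods (Table 6), and surveys every 3 months (8.3.1), hence two per period. Assumed:
- equal enrolment in each period;
- anyone with at least one completion in their first period is kept to the end, and others leave;
- no other attrition;
- individual response probabilities p follow a beta distribution with mean 0.40 and within-person correlation ρ of 0.2, 0.4 or 0.6.

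**Step 1: who is retained.** The probability of no completion in two surveys is 0.36 + 0.24ρ. The retained fraction is r = 1 − (0.36 + 0.24ρ).

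**Step 2: retained responders.** With a = 0.4(1 − ρ)/ρ, b = 0.6(1 − ρ)/ρ and s = a + b, the expected completion contributed per survey round by the retained, per person originally enrolled, is g = 0.4 − ab(b + 1)/[s(s + 1)(s + 2)]. Their mean completion rate is g/r.

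For ρ = 0.2: a = 1.6, b = 2.4, s = 4, so g = 0.4 − 13.056/120 = 0.2912 and g/r = 0.2912/0.592 = 49.2%.

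**Step 3: pooled completion.** Period 4 is (0.4 + 3g)/(1 + 3r). The whole study is (1.6 + 6g)/(4 + 6r).

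| ρ | r | g | Retained rate | Period 4 | Whole study |
|---|---|---|---|---|---|
| 0.2 | 0.592 | 0.2912 | 49.2% | 45.9% | 44.3% |
| 0.4 | 0.544 | 0.3218 | 59.2% | 51.9% | 48.6% |
| 0.6 | 0.496 | 0.3496 | 70.5% | 58.2% | 53.0% |

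The new-enrolee rate is 40% throughout. If every patient responds independently at 40% (ρ = 0), the pooled rate is also 40% in every period.

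**Step 4: standard errors for person-level predictors.** Retained members of the first three cohorts get 8, 6 and 4 surveys; everyone else gets 2. So Σm = 8 + 12r and Σm² = 16 + 104r. The design effect is 1 + (Σm²/Σm − 1)ρ, the SE ratio is its square root, and the type I error is 2Φ(−1.96/SE ratio).

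| ρ | Σm²/Σm | Design effect | SE ratio | Type I error |
|---|---|---|---|---|
| 0.2 | 77.568/15.104 = 5.14 | 1.83 | 1.35 | 14.7% |
| 0.4 | 72.576/14.528 = 5.00 | 2.60 | 1.61 | 22.4% |
| 0.6 | 67.584/13.952 = 4.84 | 3.31 | 1.82 | 28.1% |

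This formula treats the number of surveys as unrelated to response, which is not so here. Simulating the same panel directly gave somewhat smaller inflation in the same direction, so the last two columns are approximate and lean high.

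**Step 5: precision from total responses.** Take 275 enrolees per period, so 275 × 0.40 = 110 first completers per cohort. Assume 70% repeat completion, two rounds per period and a correlation of 0.3 between one person's answers. Mean completes per person are 5.9, 4.5, 3.1 and 1.7 across the four cohorts, or 110 × 15.2 = 1,672 responses at one facility. The design effect is 1 + (67.56/15.2 − 1) × 0.3 = 2.03. The half-width is ±2.4% if responses are treated as independent and ±3.4% with the design effect. Over repeat completion of 40% to 90%, one or two rounds per period, and correlation of 0.1 to 0.5, the correct interval is 1.04 to 1.80 times the naive one.

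**The case against.** The strongest reply is that the text is silent rather than wrong. Section 8.2.1 does not say that non-completers are removed, and 8.5.1 does not say that the unit is the survey. Table 2 words the metric as a proportion of patients; with one record per patient, repeated responses would not be counted as independent. This stands in part, and it is why the conclusion is conditional on a per-survey analysis. It is not a full answer: 8.3.1 counts surveys sent, started and completed, 8.5.1 bases precision on total responses, and the new-only restriction in 8.2.1 is not carried into 8.5.1.

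The size also rests on quantities that the documents do not give, and attrition among retained patients is ignored. Both points stand.

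Four stronger readings are tempting but not supported.
- A reader might infer a rising completion trend that would be taken for better implementation. Section 8.5.1 does not list study period as a factor, whereas 8.5.2 does for the exit survey, and no intervention-versus-control contrast of SMS completion is planned. The Period 4 figures would be seen only if someone tabulated by period.
- A reader might think that the ±10% is too narrow. It rests on new completes and is sound.
- A reader might extend the point to the facility dashboard. The supplement's intervention description has SMS surveys sent within three days of a visit, not to a 3-monthly panel, and the dashboard also draws on exit surveys. Nothing in the documents links the tendency to respond with reported experience.
- A reader might apply eight surveys to everyone at ρ = 0.6, giving an SE ratio of √(1 + 7 × 0.6) = 2.28 and type I error near 39%. Under the retention rule only r/4, or 12% to 15%, of participants reach eight surveys.

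**Conclusion.** The point holds in a limited form. Retention implied to depend on completion, repeat surveys, an undivided denominator and clinic-only random effects together give an overstated completion rate and understated standard errors if the analysis is per survey. Under the stated assumptions, overall completion reads about 44% to 53% against 40% among new enrolees. Standard errors for person-level predictors are understated by a factor of about 1.35 to 1.8, with type I error of about 15% to 28%. The completion bias shrinks to nothing as differences between patients disappear.

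The reach is the Objective 1 implementation metrics. SMS is not among the four modalities listed for Objective 2 in protocol 5.1, and it is not an outcome in the SAP. This is a cheap improvement to a descriptive analysis, not a threat to the trial's main conclusions.

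**What to change.** In protocol 8.5.1:
- State whether completion is counted per patient or per survey, and what happens to enrolees who do not complete.
- Report completion separately for newly enrolled and retained participants, and by period if results are tabulated over time.
- Add a participant random effect nested in clinic to the response models, or use a participant-clustered variance.
- Base precision on distinct patients, or on a response count divided by the design effect.

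The cost is analysis wording. Enrolment under 8.2.1 already records the ART number and is organised by six-month period, so no new data should be needed. Intervals become somewhat wider, and the new-enrolee estimate uses fewer surveys.

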### *8.2.2 Exit Survey (Population for Objective 1)*

The exit interview will aim to capture the patient experience among patients currently in care who are 18 years or older. Among patients leaving the facility after attending clinic that day, we will take a systematic (every kth) sample of patients to assess their experience in clinic that day, where k depends on the facility volume. Patients will be approached by study staff using a recruitment script to determine their eligibility and voluntary willingness to participate. If they agree, we will collect their ART number, and thereby be enumerated for the exit survey. We seek to collect 75-100 complete surveys per six months and estimate the patient experience with a precision of approximately +/-10%. Many patients will be given the opportunity to participate in both the SMS and exit surveys.

For both the SMS Surveys and Exit Surveys we seek a waiver of consent. The questions posed in the SMS and exit surveys involve minimal risk to the participants and are designed to not reveal anything about individual HIV care. They are similar to consumer satisfaction surveys used across various industries. They are also similar to data recorded during programmatic standard of care tracing of late or lost patients that are connected to their

electronic medical record data. Participants are free to not respond to any questions in the exit survey or to not respond to the SMS, even if they do agree to voluntarily participate. As the surveys are short (3-13 questions) and conducted after the patient has sought care, the greatest time burden on the participant would be a written consent process. By relieving this time burden in a minimal risk environment, the study will likely permit more patients to share their care experiences, which has been shown to be desirable in both formative and pilot data collection.

### 8.2.3 *BetterInfo Lite (Population for Objective 1)*

The target population for *Better Info Lite* procedures are patients who are currently LTFU according to facility practices. Of note, the tracing of lost to follow-up patients and recording of their vital status and barriers to care is now a priority for all sites from donors and the Zambian MOH, and is therefore considered standard of care. We will support this existing tracing being conducted routinely at study sites and this will include all data on patient reported reasons for engagement or disengagement. Our support to the facility will include sharing our experience on the BetterInfo study and ensuring facility staff are well trained on ensuring tracing outcomes are met. We will also support facilities if needed to identify patients that are lost to follow up using the Better Info algorithm (REF. No 004-06-14) as well as to revise facility specific retention estimates based on facility tracing outcomes. If further intensive tracing is required or desired by the facility to obtain more accurate outcome estimates for program reporting (again this is outside of the research and routinely mandated clinical reporting), among those LTFU patients, we will assist with selecting of a random sample currently LTFU using existing standards (REF. No 004-06-14).

### 8.2.5 *Training Curriculum and Coaching (Population for Objective 1)*

The target population for the training curriculum and coaching component of our intervention are all health care workers at our study facilities. This includes medical officers, clinical officers, nursing staff, lay health workers/counsellors, pharmacists, data managers, and others. We anticipate approximately an average of 20 health care workers across these widely varying clinics, for a total of 800 health care workers targeted for training. Assessment will be made both quantitatively (e.g., people trained, the frequency of coaching visits to the target facilities, health care worker experience survey) as reported in Coaching Logs, as well as qualitatively (e.g., how did the health care workers at our study facilities feel about the coaching, how did the study coaches feel about the coaching, what did it entail, what are patient perceptions of the intervention outcomes.) as understood through interviews with patients, focus group discussions with health care workers, what are facility vital signs that affect operations and observations at the facilities. Finally, we will assess the implementation of the incentive schema during intervention periods as understood through coaching logs or other administrative records documenting rewards given and facility performance, and FGDs with health care workers. At a high level, we will assess whether all facilities participated in the incentive schema, but will also employ mixed quantitative and qualitative methods to understand how health care workers perceived the incentive program.

*Table 2: Sample size by Activity (Population for Objective 1)*

| Approach   | Depth | Reach | Purpose/Use                                                                                                                                                                                                      | Sample Size                                                                                                                                                 | Implementation metrics                                                     |
|------------|-------|-------|------------------------------------------------------------------------------------------------------------------------------------------------------------------------------------------------------------------|-------------------------------------------------------------------------------------------------------------------------------------------------------------|----------------------------------------------------------------------------|
| SMS survey | +     | +++++ | SMS will be critical due to speed and reach. In addition, it will allow for potential capture of care experiences that occur in community that are not captured by exit surveys in facility based models of care | Up to average 200 measurements in each of approximately 34 facilities in each of the four study periods (200 * 34 * 4) for total maximum of 27,200 measures | Proportion of patients who agree to, receive, initiate and complete survey |

|                                     |    |     |                                                                                                                                                                                   |                                                                                                                                                                                  |                                                                                                                                                                                                                                    |
|-------------------------------------|----|-----|-----------------------------------------------------------------------------------------------------------------------------------------------------------------------------------|----------------------------------------------------------------------------------------------------------------------------------------------------------------------------------|------------------------------------------------------------------------------------------------------------------------------------------------------------------------------------------------------------------------------------|
| Exit survey                         | ++ | +++ | Exit survey will provide the opportunity to reach a larger number of patients immediately after their contact with the health system when recall bias is minimized.               | Up to average of approximately 75-100 -measurements in each of 34 facilities in each of the four study periods (100 * 34 * 4) for total maximum of approximately 13,600 measures | Proportion of patients approached who agree to do, and complete survey                                                                                                                                                             |
| Enhanced Tracing (Better Info Lite) | ++ | +++ | Leveraging on already existing enhanced tracing and surveying patients who are LTFU will be essential to capturing the patient experience of those who have disengaged from care. | As per routine facility tracing guidelines                                                                                                                                       | 
The fraction of patients the facility identify for tracing that are attempted
 
The fraction contacted and vital status updated
 
The fraction with adequate documentation of reasons who are contacted in person
 |

### 8.3 Data collection for Objective 1

